## Abstract

**Background:**

SARS-CoV-2, the virus that causes COVID-19, enters the cells through a mechanism dependent on its binding to angiotensin-converting enzyme 2 (ACE2), a protein highly expressed in the lungs. The putative viral-induced inhibition of ACE2 could result in the defective degradation of bradykinin, a potent inflammatory substance. We hypothesize that increased bradykinin in the lungs is an important mechanism driving the development of pneumonia and respiratory failure in COVID-19.

**Methods:**

This is a phase II, single-center, three-armed parallel-group, open-label, active control superiority randomized clinical trial. One hundred eighty eligible patients will be randomly assigned in a 1:1:1 ratio to receive either the inhibitor of C1e/kallikrein 20 U/kg intravenously on day 1 and day 4 plus standard care; or icatibant 30 mg subcutaneously, three doses/day for 4 days plus standard care; or standard care alone, as recommended in the clinical trials published to date, which includes supplemental oxygen, non-invasive and invasive ventilation, antibiotic agents, anti-inflammatory agents, prophylactic antithrombotic therapy, vasopressor support, and renal replacement therapy.

**Discussion:**

Accumulation of bradykinin in the lungs is a common side effect of ACE inhibitors leading to cough. In animal models, the inactivation of ACE2 leads to severe acute pneumonitis in response to lipopolysaccharide (LPS), and the inhibition of bradykinin almost completely restores the lung structure. We believe that inhibition of bradykinin in severe COVID-19 patients could reduce the lung inflammatory response, impacting positively on the severity of disease and mortality rates.

**Trial registration:**

Brazilian Clinical Trials Registry Universal Trial Number (UTN) U1111-1250-1843. Registered on May/5/2020.

## Introduction

### Background and rationale {6a}

The acute respiratory illness caused by SARS-CoV-2 infection has been confirmed in + 3.3 million patients, leading to the deaths of more than 70,000 people worldwide (WHO official records as of May 1, 2020). Currently, patients are treated with a combination of respiratory support, large spectrum antibiotics, and eventually extracorporeal oxygenation [2]; however, the outcomes are unsatisfactory. On March 18, 2020, the first clinical trial of antiviral agents (lopinavir-ritonavir) was published revealing no benefits in hospitalized adults with severe COVID-19, as compared with standard care [3]. Thus, the search for therapeutic strategies that could reduce the severity and high mortality rates of COVID-19 is an important issue in public health.

One of the intriguing aspects of COVID-19 is that hypertension and diabetes are the most important risk factors for severe progression and mortality, exceeding by far chronic obstructive pulmonary disease and asthma, which could intuitively be regarded as the preexisting disorders with the highest risk for unfavorable COVID-19 progression [2, 4]. We asked whether the mechanisms related to the viral infection could explain the high association between severe progression of COVID-19 and hypertension and diabetes. We found that SARS-CoV, responsible for the outbreak of SARS during the early 2000s, uses the enzyme ACE2 as a receptor for human cell entry [5]; in addition, a study published on March 6, 2020, revealed that SARS-CoV-2 also binds to ACE2, using the same mechanism to enter cells [6].

ACE2 catalyzes the inactivation of angiotensin II (AII) [7], and its putative inhibition by SARS-CoV-2 could result in increased systemic levels of AII. Patients with both hypertension and diabetes have abnormalities in the renin-angiotensin system, and this could increase the risk of circulatory, renal, and electrolytic abnormalities that, hypothetically, could result in increased severity of COVID-19.

However, the detailed evaluation of clinical and laboratory records from patients with severe COVID-19 shows low rates of circulatory abnormalities (shock was present in only 13% of patients with severe evolution of the disease), kidney failure (6%), and electrolytic abnormalities (virtually absent). These findings strongly suggest that increased AII levels do not explain the severity of the illness [2].

Another important function of the ACE system is the inactivation of the potent inflammatory substance bradykinin [8]. Accumulation of bradykinin in the lungs is a common side effect of ACE inhibitors leading to cough [9]. In animal models, the inactivation of ACE2 leads to severe acute pneumonitis in response to lipopolysaccharide (LPS), and the inhibition of bradykinin almost completely restores the lung structure [10].

In COVID-19 patients, rapidly progressing pneumonia is the main clinical feature associated with severe outcomes [2]. This is accompanied by high levels of C-reactive protein, indicating the magnitude of the inflammatory response [2]. Thus, we hypothesized that increased bradykinin, and not AII, is the main link between SARS-CoV-2 inhibition of ACE2 and severity of the disease. The abnormalities of the ACE system in hypertensive and diabetic patients, potentially associated with the chronic use of ACE inhibitors, could predispose to a massive increase in lung bradykinin leading to rapidly progressing pneumonia.

Currently, inhibition of bradykinin is the main therapeutic approach to treat a rare disease known as hereditary angioedema [11]. There are three major pharmacological approaches used to dampen bradykinin activity: (i) inhibition of bradykinin synthesis using either the human-derived inhibitor of C1e/kallikrein [12] or (ii) a synthetic inhibitor of kallikrein [13] and (iii) inhibition of bradykinin receptor 2 [14]. We propose the ITHACA trial (COVID-19 Treated by c1 esterase inHibitor And iCAtibant) to assess the efficacy and safety of the inhibitor of C1e/kallikrein and the inhibitor of bradykinin receptor 2 compared to standard care alone in the treatment of patients with pneumonia caused by COVID-19. We have designed a three-arm study to increase efficiency and reduce costs, since the same control arm will be used for comparison with two different drugs. In addition, this design increases the likelihood that the participant will be allocated to a treatment arm, which usually increases the chance of enrollment.

### Objectives {7}

The objective is to evaluate the efficacy and safety of each C1 esterase inhibitor plus standard care and use of icatibant plus standard care vs. standard care alone in hospitalized adult patients with pneumonia caused by COVID-19.

### Trial design {8}

This is a phase II/II, single-center, three-armed parallel-group, open-label, active control superiority, randomized clinical trial. We will use a 1:1:1 allocation ratio to C1 esterase inhibitor plus standard care vs. icatibant plus standard care vs. standard care alone. This study will follow the principles of the Declaration of Helsinki. The trial design is depicted in Fig. 1.

**Fig. 1 Fig1:**
[figure not shown]
Graphic representation of the Ithaca Study design

## Methods: participants, interventions, and outcomes

### Study setting {9}

This is a single-site study, and all procedures will be conducted at the Clinical Hospital at the University of Campinas in wards and intensive care units specifically focused on the care of patients with COVID-19. The expected enrollment start date is April 21, 2020, and the expected end date is July 21, 2020.

### Eligibility criteria {10}

Once all inclusion criteria have been met and the patient’s physician agrees to the patient’s participation in the study, a study staff member will apply the consent form and only then will the patient be included in one of the three study arms according to the randomization procedures.

The drugs under study, as well as the standard care treatment, will be prescribed by the attending physician of the hospital.

The following are the inclusion criteria:
Patients aged ≥ 18 years at the time of signing the consent form≤ 12 days since the onset of the symptoms until the start of the treatmentSARS-CoV-2 diagnosis by RT-PCR methodPneumonia confirmed by computed tomography of the chestHospitalized patients with a SpO_2_ ≤ 94% in ambient air or PaO_2_/FiO_2_ ≤ 300 mmHgThe willingness of study participants to accept randomization to any assigned treatment armThe patient or responsible (in the case of incapacitated adults) must have signed the consent formThe patient must agree not to enroll in any other experimental study prior to completing the 28-day follow-up

The following are the exclusion criteria:
Pregnancy or breastfeeding (pregnancy beta-HCG test will be performed in women of childbearing age).Known severe renal impairment (estimated glomerular filtration rate ≤ 30 ml/min/1.73 m^2^), patients receiving continuous renal replacement therapy (hemodialysis or peritoneal dialysis), or previous renal transplant.Known severe liver disease (AST or ALT 5× above the reference value).Patients diagnosed with HIV infection or patient with any other immunodeficiencies.Patients with a previous diagnosis of cancer.Patients with a previous diagnosis of hereditary angioedema.Patients with previous ischemic myocardial disease.Patients with previous thromboembolic disease.The assisting physician considers that the participation of the patient in the study is not appropriate, either because it is not of clinical interest or because of any condition that does not allow the protocol to be followed safely.The patient will be transferred to any other hospital before the 28 days of follow-up or before discharge from the hospital.Receipt of any experimental treatment for COVID-19 virus infection within 30 days prior to molecular screening.

### Who will take informed consent? {26a}

Study staff will obtain signed informed consent from the eligible patient or the responsible (in the case of incapacitated adults). The responsible will be the spouse/husband (or partner) unless there has been a legal or de facto separation, as determined by Art. 1.775 of the Brazilian Civil Code. In the absence of such persons, the burden will fall on the parents or descendants.

### Additional consent provisions for collection and use of participant data and biological specimens {26b}

The consent form contains provisions for the collection of research data and blood samples for the current study, but eventual ancillary studies, which could utilize the material stored in a biorepository, will be subject to the participant’s prior consent and approval of the new project by the local research ethics committee.

## Interventions

### Explanation for the choice of comparators {6b}

This study will have two active arms. The first one is C1 esterase inhibitor plus standard care. The second study arm is icatibant, a bradykinin receptor 2 inhibitor, plus standard care. Our hypothesis is that increased bradykinin is the main link between SARS-CoV-2 infection and inhibition of angiotensin 2-converting enzyme (ECA2), resulting in respiratory failure. Therefore, we chose the C1 esterase inhibitor and icatibant because they are the only two drugs that act in the inhibition of bradykinin that have been approved in Brazil. Both drugs are currently approved for use in humans for the treatment of hereditary angioedema, with good efficacy and a low side effect profile.

To date, there is no effective treatment for pneumonia caused by COVID-19 to include as an active control comparator. Thus, the third arm, which will be the comparator for the first two, will comprise standard care alone. The standard care will always involve the use of antibiotics intravenously and prophylactic antithrombotic therapy. Oxygen support, non-invasive and invasive mechanical ventilation, vasopressor use, and renal support therapy will also be provided as part of standard care, but will be used according to medical judgment.

Given that the COVID-19 pandemic is an emergency health problem worldwide, we chose not to use a placebo, since its formulation would delay the study schedule and increase costs.

### Intervention description {11a}

#### Group A (experimental) plus standard care

Firazyr® [Icatibant acetate 30 mg (with a concentration of 10 mg/mL—total 3 ml)] prefilled syringe delivers 30 mg of icatibant as icatibant acetate. Subcutaneous injection in the abdominal area was administered at intervals of 8 h for 4 days. This dose has been used successfully for the management of ACE inhibitor-induced angioedema and hereditary angioedema {Baş, 2015, A randomized trial of icatibant in ACE-inhibitor-induced angioedema}{Cicardi, 2010, Icatibant’, a new bradykinin-receptor antagonist’, in hereditary angioedema}. Drug-related adverse events occurred in 14–15% of the individuals receiving icatibant in the FAST-1 and FAST-2 trials, mainly injection site reaction, although with 11% of serious adverse events in FAST-2 trial, which were gastroenteritis and hypertensive crisis, laryngeal attack of angioedema requiring intubation, abdominal attack of angioedema, and cholelithiasis.

#### Group B (experimental) plus standard care

Berinert® [plasma-derived C1 esterase inhibitor (human)] will be administered at a dose of 20 IU/kg body weight on day 1 shortly after recruitment and on day 4. Each vial contains 500 IU of C1 esterase inhibitor as a lyophilized product for reconstitution with 10 mL of sterile water for injection, USP provided, following datasheet instructions. Berinert® is indicated for the treatment of acute hereditary angioedema (HAE) attacks at a dose of 20 IU/kg. The IMPACT-1 trial established the efficacy and security of Berinert® 20 IU/kg compared with placebo [15]. The most commonly observed adverse events reported on the Berinert® prescribing information are gastrointestinal symptoms [16]. Among 125 subjects enrolled in the IMPACT-1 trial, the treatment-related severe adverse reactions that occurred in 5 individuals treated with 20 IU/kg body weight were laryngeal edema, facial attack, swelling, exacerbation of hereditary angioedema, and laryngospasm.

#### Group C (active control)

The standard care will always provide antibiotics intravenously and prophylactic antithrombotic therapy. Oxygen support, non-invasive and invasive mechanical ventilation, vasopressor use, and renal support therapy will also be provided as part of standard care, but only according to medical judgment.

### Criteria for discontinuing or modifying allocated interventions {11b}

Withdrawal of consent. This item follows the Declaration of Helsinki, in which the patient has the right to withdraw his consent without any prejudice regarding the treatment offered to him/her by the clinical provider.Grade 4 adverse reaction (life-threatening consequences) as stated by Common Terminology Criteria for Adverse Events (CTCAE) v6.0 used for oncology drugs by the National Cancer Institute (NCI).Protocol violation.Allergic reactions to any drug or any other situation deemed to jeopardize patient safety.

### Strategies to improve adherence to interventions {11c}

We consider that it is not necessary to draw up a plan of adherence to the interventions, since the patient will be hospitalized for the entire follow-up time and the healthcare professionals will administer the drugs (intravenous or subcutaneous) and standard care according to medical prescription.

### Relevant concomitant care permitted or prohibited during the trial {11d}

All usual intensive care management procedures are permitted and will be determined by the clinical providers, in accordance with the Asian Critical Care Clinical Trials Group [17], but the patient will not be allowed to be on another experimental protocol, e.g., chloroquine or others.

### Provisions for post-trial care {30}

The patients in our study will receive the most suitable standard care treatment, plus the proposed medicines, according to the allocation arm, and will be monitored by the medical team of the Clinics Hospital of the University of Campinas during the 28 days of follow-up (or hospital discharge), or as long as necessary. Therefore, patients will receive medical care during the trial follow-up itself in relation to serious adverse events (SAE). Regarding adverse events in general, we also believe that most of them should occur during this period; however, the post-trial care of the patient is ensured through free care at the Clinics Hospital of the University of Campinas, both via the emergency room and outpatient care, following the principle of universality of the Brazilian Health System (SUS).

Regarding the results on efficacy, if there is a positive impact of any of the medications investigated on hospitalized patients, the benefit on the participants of the study will be assessed during the follow-up period. During the trial, we intend to maintain a dialog with competent health authorities (at municipal, state, and federal levels) in order to enable the negotiation of more affordable prices for medicines, as well as coordinate their acquisition and distribution to the target patients.

### Outcomes {12}

#### Primary outcome

Time to clinical improvement (TTCI)—the TTCI was defined as proposed by the Cap-China Network [18] and thereafter utilized in the LOTUS China trial [3] and recommended by the World Health Organization (WHO) [19]. Briefly, TTCI refers to the time from randomization to an improvement of two points on the seven-category ordinal scale stated below [3] or live discharge from the hospital:
Not hospitalized with the resumption of normal activitiesNot hospitalized, but unable to resume normal activitiesHospitalized, not requiring supplemental oxygenHospitalized, requiring supplemental oxygenHospitalized, requiring nasal high-flow oxygen therapy and non-invasive mechanical ventilationHospitalized, requiring ECMO, invasive mechanical ventilation, or bothDeath

#### Secondary outcomes

Percentage of patients on a seven-category scale on days 7, 14, and 21Duration (days) of mechanical ventilationDuration of hospitalization (days) of survivorsNeed for oxygen support (days)Time from randomization to hospital discharge (days)Time from randomization to death (days)Occurrence of acute kidney injury, defined as an increase in creatinine 1.5 times above the baselineFrequency of severe adverse events as defined by the National Cancer Institute Common Terminology Criteria for Adverse Events (CTCAE), version 5.0

### Participant timeline {13}

The participant timeline is depicted in Table 1.

**Table 1 Tab1:** Timeline of events in the trial

	Enrollment	Allocation	Post-allocation				Discharge	Close-out
Time point	− 1	0	D1–D4	D5–D7	D8–D14	D15–D28		
Enrollment								
Screening	x							
Eligibility criteria	x							
Informed consent	x							
Allocation		x						
Randomization		x						
Baseline data collection		x						
Interventions								
Icatibant/std care			x					
C1 inhib./std care			x					
Std care	x	x	x	x	x	x	x	
Outcome/safety assessments								
CT of the chest	x				X (D14)	X (D28)	X	
Primary outcome			x	x	x	x	x	
Clinical symptoms		x	x	x	x	x	x	
Vital signs	x	x	x	x	x	x	x	x
ECG				x				
Adverse events	x	x	x	x	x	x	x	x
Time mechanical ventilation								x
Death								x
Length of stay								x
Laboratory tests*	Only every 4 days or at the discretion of the assistant physician							
RT-PCR SARS-CoV-2	x							
Bradykinin		x	x				x	
SOFA score		x	x	x	x	x	x	
Blood routine		x	x	x	x	x	x	
Coagulation routine		x	x	x	x	x	x	
CRP		x	x	x	x	x	x	
Liver function		x	x	x	x	x	x	
Kidney function		x	x	x	x	x	x	
d-dimer		x	x	x	x	x	x	
High-sensitivity troponin		x	x	x	x	x	x	
Pro-BNP		x	x	x	x	x	x	
Aspergillus antigen		x	x	x	x	x		

### Sample size {14}

We used information from the previously published LOTUS [3] trial evaluating the effect of lopinavir-ritonavir on time to clinical improvement (TTCI) [censored at day 28], since there is no information on the effect of icatibant or C1 esterase inhibitor for this primary outcome. This approach resulted in a hazard ratio of 1.24 for clinical improvement. It is also relevant to take into account the emergency situation and the high costs involved. The sample size was determined based on the formula for the proportional hazard regression model (Schoenfeld, 1983). We assumed a 5% type 1 error (alpha), power test of 80%, drop-out (censure) rate of 20%, and hazard ratio between treatment and the standard care alone varying from 1.2 to 2.0. To extend the calculations for a three-arm trial, we considered the three groups of the same size and the comparison of the two treatments separately to standard care alone, but without comparing the two treatments to each other. In other words, the same standard care alone group will be compared with each treatment group. Additionally, we set alpha at 2.5% to allow for multiple testing and multiplied the sample size by 1.5. Figure 2 presents the total sample size required for this setup and according to different hazard ratios. Assuming a hazard ratio of 1.9, we obtained a final sample size of 174 (58 per group).

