## Statistical methods

### Statistical methods for primary and secondary outcomes {20a}

All our statistical analyses will follow the intention-to-treat principle. For the primary outcome, we will use the Kaplan-Meier estimator and log-rank test to respectively estimate and compare the survival curves, followed by a Cox proportional hazards model to adjust for baseline explanatory variables in the final data analysis. Multiple imputation will be used to impute missing data. The following covariates will be settled: age, sex, duration of symptoms before enrollment, use of oxygen support prior to enrollment, and presence of relevant comorbidities. This analysis will be performed to compare each treatment arm, that is, the icatibant plus standard care group and the C1 esterase group inhibitor plus standard care, with the standard care group alone. In the analysis of secondary endpoints involving time to event, such as duration of mechanical ventilation (days) and length of hospitalization in survivors (days), we will also use the Cox proportional hazards model. The logistic regression model will be used to analyze secondary binary endpoints.

The statistical analysis plan (SAP) containing all the details of the analysis will be finalized and made available to the DSMC before the final analysis.

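### The only multiplicity rule stated is a fixed 2.5% for each drug; Holm's step-down test would give more power at the same 5% family-wise error and the same 174 patients

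*Protocol article*

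**What the plan says.** The protocol article, Sample size {14}, starts from a 5% type 1 error and 80% power. Each of the two treatments is compared with the same standard-care group, and the two treatments are not compared with each other. For the three arms it then states: "Additionally, we set alpha at 2.5% to allow for multiple testing", and it scales the two-arm size by 1.5. At a hazard ratio of 1.9 this leads to 174 patients, 58 per group.

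Statistical methods {20a} sets out a log-rank test and a Cox model for time to clinical improvement and adds: "This analysis will be performed to compare each treatment arm" with standard care. It gives no significance level and no rule linking the two tests, and it refers the details to a statistical analysis plan that is not shown. The 2.5% in the sample size section is therefore the only multiplicity rule in the document.

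Interim analyses {21b} plans one look for effectiveness, futility and safety at half of the events and states no boundary.

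**The concern.** If each comparison is judged at 2.5% whatever the other shows, part of the 5% family-wise error goes unused. Once one drug has been shown to work at 2.5%, only one hypothesis is left that could be rejected falsely, and it can be tested at the full 5%.

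This bears on the present trial because the rationale rests on one mechanism, bradykinin excess, for both drugs. If that mechanism matters, both drugs may work, which is where a step-down test gains most. Under a fixed 2.5%, a second drug with p = 0.03 would be declared negative even though the first had succeeded and the 5% family-wise error would allow the claim.

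**Working it through.** **Inputs from Sample size {14}:** hazard ratio 1.9; alpha 5%, set at 2.5% per comparison; power 80%; drop-out or censoring 20%; multiplier 1.5 for the third arm. Allocation is 1:1:1 (Trial design {8}). Sidedness is not stated.

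**1. Reproduce 174.** Schoenfeld's formula for two equal arms is events = 4(z_α + z_β)² / (ln HR)².
- Two-sided 2.5%: z_α = 2.241; 80% power: z_β = 0.842; ln 1.9 = 0.642.
- Events = 4 × (2.241 + 0.842)² / 0.642² = 92.29.
- Patients in two arms = 92.29 / 0.8 = 115.4, rounded up to 116.
- Three arms = 116 × 1.5 = 174, or 58 per group. This is the article's figure.

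Two-sided 5% or one-sided 2.5% gives about 143 to 146, and one-sided 5% about 113 to 116. The sample size therefore rests on a two-sided 2.5% test per comparison.

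**2. Holm keeps the family-wise error.**
- Both nulls true: a false claim needs the smaller p-value to be at most 0.025. The probability is at most 2.5% + 2.5% = 5%.
- One null true: a false claim needs that null's own p-value to be at most 0.05. The probability is at most 5%.

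Every rejection at 2.5% is kept, so Holm cannot lose power. Its first step is the test that gave 174, so the sample size does not change.

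**3. Size of the gain.** The planned events per comparison are 116 × 0.8 = 92.8. The mean of each test statistic is ln(HR) × √(92.8/4), which is 3.09 at HR 1.9. With equal arms and a shared control, the correlation is 1/(1 + 1) = 0.5. Simulating 3,000,000 pairs of normal test statistics, without an interim look, gave (error about 0.03 points or less):

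| True hazard ratios | Quantity | Fixed 2.5% | Holm |
|---|---|---|---|
| 1.9 and 1.9 | power per drug | 80.3% | 84.8% |
| 1.9 and 1.9 | power for both | 69.1% | 78.1% |
| 1.9 and 1.9 | at least one | 91.5% | 91.5% |
| 1.9 and 1.5 | power, weaker drug | 38.6% | 48.2% |
| 1.9 and 1.5 | power, stronger drug | 80.3% | 81.5% |
| 1.9 and 1.0 | power, effective drug | 80.3% | 80.4% |
| 1.9 and 1.0 | false claim for the other | 2.5% | 4.25% |
| 1.24 and 1.24 | power for both | 3.9% | 6.7% |
| 1.0 and 1.0 | any false claim | 4.64% | 4.64% |

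With the 180 patients named in the abstract (96 events per comparison) and both hazard ratios at 1.9, power per drug goes from 81.7% to 86.1%, and power for both from 71.1% to 79.8%.

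**The case against.** The strongest reply is that nothing here is wrong. Bonferroni controls the family-wise error, and 2.5% is also the right level at which to size Holm's first step. The 2.5% stands only in the sample size section. A reader might infer that the final tests are irrevocably fixed at 2.5%, but the analysis section gives no test level, and the unseen analysis plan could adopt Holm without changing the 174. That stands. The point is limited to this: the one rule the article states is less efficient than an alternative that costs no patients.

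A reader might also take success with both drugs to be the aim. The objectives evaluate each drug against standard care, and no section makes joint success a goal. Power for both is therefore a way to show the gain, not a planned quantity. The gain also depends on the truth. It is small if only one drug works, and at the hazard ratio of 1.24 that the article takes from an earlier trial of another drug, power is low under either rule.

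The change has a small cost. A second drug with p between 0.025 and 0.05 would be declared effective while its 97.5% confidence interval includes a hazard ratio of 1. It should not be assumed that 97.5% intervals are planned, since the article specifies none.

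Nor does the article give an interim boundary into which the second test could be fitted. Without one, the 5% family-wise level is not assured under Bonferroni or Holm.

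**Conclusion.** The point holds as an optional improvement in efficiency. The stated split of 5% into 2.5% per comparison is valid, but Holm does at least as well in every case. With both drugs at the planned hazard ratio of 1.9, the gain is 4.5 points per drug (84.8 − 80.3) and 9.0 points for both (78.1 − 69.1). With hazard ratios of 1.9 and 1.5, the weaker drug gains 9.6 points (48.2 − 38.6). If only one drug works the gain is 0.1 to 0.2 points, and the chance of at least one success never changes.

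These figures assume two-sided tests (inferred from the 174), 92.8 events per comparison, a correlation of 0.5 and approximately normal test statistics. They also assume that the efficacy interim spends no alpha that is not accounted for. The documents do not support reading this as an error in the sample size or a failure of error control caused by the 2.5% split.

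**What to change.** Add one sentence to Statistical methods {20a} and carry it into the analysis plan, before results by arm are seen: the smaller of the two primary p-values is tested at two-sided 2.5% and, if it is significant, the other is tested at two-sided 5% (Holm). Leave the sample size at 174.

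State in the report that any 97.5% intervals are not matched to the step-down test, so an interval that includes 1 can accompany a claim of effect for the second drug. Whatever interim efficacy rule is adopted should account for its alpha at both steps.

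The change needs no further patients, visits or data. The cost is the wording, that mismatch, and an amendment for ethics review, because the article requires one for changes to the statistical analysis.
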